### Data quality assurance

Data collection tools were pretested and revised as necessary before use. A data management plan for the study is in place to assure data quality at all stages. The key components of the plan include the use of logic checks and skip patterns; verification of completeness of each record by POs prior to server upload; verification by POs of a random 20% of study subjects with submitted survey data that surveys were in fact administered to them; and real-time data review and monitoring by study investigators based in Kenya, Nigeria, and USA on the REDCap
^TM^ cloud platform. In Nigeria, where women tend to deliver at the same facility where they receive ANC, POs also cross-checked 20% of self-reported facility-based deliveries with facility records. This verification was not possible in Kenya where women commonly seek ANC and delivery care at different facilities, including the private sector.

### Anticipated and unanticipated events

We have no reason to believe that the intervention will cause harm. However, there might be some risk of embarrassment to women who share their personal information with group members; such information might leak outside the group. Additionally, the study team is tracking occurrence of anticipated and unanticipated events as outlined in the research plan. These include miscarriages, stillbirths, neonatal deaths, and maternal deaths.

### Data analysis

Data analysis and the reporting of results for this study will be conducted in accordance with norms for analyzing cluster randomized trials as described in the Consolidated Standards of Reporting Trials guidelines
^53^.

***Quantitative data analysis.*** Descriptive analysis of quantitative variables will be done using measures of central tendency (mean, median), measures of dispersion (range, standard deviation), and proportions (frequencies, percentages) as appropriate. Next, differences between the two study arms will be assessed using chi square test. Potential confounding factors, such as the women’s age will be assessed.

The primary outcome analysis will be done based on the intention-to-treat analysis. Participant’s data will be analyzed based on the groups to which they were randomized to compare the proportions of facility-based deliveries between the two study arms. The endpoints will be analyzed using a generalized estimating equations multivariable logistic regression model. The model will adjust the estimates for imbalances in the baseline characteristics.

Secondary analysis will be conducted to explore the uptake of services offered at ANC and during the 12-month post-delivery period, such as FP and child immunization. All statistical analysis will be performed using the
R statistical software
^54^. Subgroup analysis will be conducted for specific subgroups to determine if there was a differential effect of the interventions. The amount of missing data will be assessed for each variable and overall for the sample. If more than 5% of data are missing, multiple imputation methods will be used, assuming data are missing at random
^55^.

***Qualitative data analysis.*** Following each audio recording, either the moderator or an official transcriber familiar with local language and English will transcribe from listening to the audio recording. The transcription will be done, and personal identifiers redacted. The transcribed data will be checked for quality by study staff conversant in both English and local languages used. Transcriptions will be in English. Analysis will be ongoing to inform decisions on saturation and thus there is no need to wait until all qualitative data are collected. Coding of textual passages will be done in Atlas-ti or other similar qualitative data analysis software. Two to three qualitative data analysts will code the textual information on health topics. The emerging themes will be summarized in tables and other appropriate formats. Audio recordings will be retained until when transcriptions analysis are complete, then destroyed. The electronic versions will be stored by Jhpiego in secure servers along with the electronic quantitative data files.

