## Abstract

**Background:** Antenatal care (ANC) in many low- and middle-income countries is under-utilized and of sub-optimal quality. Group ANC (G-ANC) is an intervention designed to improve the experience and provision of ANC for groups of women (cohorts) at similar stages of pregnancy.

**Methods:** A two-arm, two-phase, cluster randomized controlled trial (cRCT) (non-blinded) is being conducted in Kenya and Nigeria. Public health facilities were matched and randomized to either standard individual ANC (control) or G-ANC (intervention) prior to enrollment. Participants include pregnant women attending first ANC at gestational age <24 weeks, health care providers, and sub-national health managers. Enrollment ended in June 2017 for both countries. In the intervention arm, pregnant women are assigned to cohorts at first ANC visit and receive subsequent care together during five meetings facilitated by a health care provider (Phase 1). After birth, the same cohorts meet four times over 12 months with their babies (Phase 2). Data collection was performed through surveys, clinical data extraction, focus group discussions, and in-depth interviews. Phase 1 data collection ended in January 2018 and Phase 2 concludes in November 2018. Intention-to-treat analysis will be used to evaluate primary outcomes for Phases 1 and 2: health facility delivery and use of a modern method of family planning at 12 months postpartum, respectively. Data analysis and reporting of results will be consistent with norms for cRCTs. General estimating equation models that account for clustering will be employed for primary outcome analyzes.

**Results:** Overall 1,075 and 1,013 pregnant women were enrolled in Nigeria and Kenya, respectively. Final study results will be available in February 2019.

**Conclusions:** This is the first cRCT on G-ANC in Africa. It is among the first to examine the effects of continuing group care through the first year postpartum.

**Registration**: Pan African Clinical Trials Registry
PACTR201706002254227 May 02, 2017

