## Methods

### Study design

The study is a multi-country, two-phase, cRCT implemented in Machakos and Kisumu Counties, Kenya and in Nasarawa State, Nigeria. It was designed in collaboration with the Kenyan Ministry of Health (MOH) and the Nasarawa State MOH and Primary Health Care Development Agency in Nigeria.

In each country, 20 health facilities were selected and matched in pairs by: type of health facility (e.g., health center, hospital); client caseload for first ANC visit (i.e., ANC1); location (urban, peri-urban, rural); culturally similar catchment populations; and availability of FP services. The pairs had to be either within the same state (Nigeria) or county (Kenya), but did not need to be geographically adjacent. In Kenya, 10 clusters were assigned to each of the two counties where the study took place.

The unit of randomization was the health facility, which formed the clusters. For each pair of matched health facilities, randomization (1:1) was done to the intervention (group care) or control arm (the current standard of individual care according to country guidelines). Assignment to study arms was done through a lottery using pieces of paper in a basket bearing the words “intervention” or “control”.

In both study arms, all women provided written consent to participate in the study. In each health facility, 50–54 participants were consented and enrolled, along with three health care providers. For the intervention arm, four to five cohorts (groups of women) were formed per facility.
Figure 1 summarizes the study design.

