### Sample size

Sample size calculations were done separately for the two countries based on the assumptions that were relevant to the local situation. In each country, the goal was to ensure that the study was adequately powered and each cluster could recruit at least four cohorts.

**Quantitative:** The study is powered to detect a 15 percentage point difference in the primary outcome of interest—proportion of deliveries in a health facility—between the intervention and control arms at the end of Phase 1. For the purpose of sample size calculations, DHS data were used to estimate the average proportions of facility-based delivery in the study regions: 61% for Kenya and 40% for Nasarawa State in Nigeria respectively
^35,
36^.

Intra-class correlation was estimated at 0.03 for both countries, which will lead to a design effect of 2.45, assuming an average of 30 new ANC clients per month in Kenya and 20 new ANC clients per month in Nigeria for each of the 20 health facilities in each country (i.e., 10 facilities per study arm). After factoring an attrition rate of 20%, sample sizes of 1,026 and 1,076 women were determined for Kenya and Nigeria, respectively. The study is powered at 85% for Kenya and 80% for Nigeria to maintain enrollment sufficient for four cohorts per health facility. Three health care providers were recruited per facility (120 total), including only those who routinely provide ANC services.

For Phase 2, we calculated the change in proportion of women who are using a modern FP method at 12 months after birth that would be detectable given the sample size enrolled for Phase 1. Current estimates of PPFP use from the most recent DHS were not available for Kenya or Nigeria. For Kenya, the rate therefore was estimated at 65%, based on rates of PPFP one year after birth in the 2014 endline results from the Kenya Urban Reproductive Health Initiative
^52^. For Nigeria, sample size estimation used the contraceptive prevalence rate (modern methods) of 16% for Nasarawa State from the 2013 Nigeria DHS. Based on assumed 20% attrition in Phase 1 and an additional 20% attrition by the end of Phase 2, the study will be able to detect a 10-percentage point difference in PPFP use at 12 months in Kenya and nine percentage point difference in Nigeria between study arms.

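### The chi-square comparison of the arms ignores facility clustering; at the plan's own ICC, any p-value taken from it has a false-positive rate of about 16–22% rather than 5%

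*Protocol article*

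**What the plan says.** All references are to the protocol article.

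- **Study design.** "The unit of randomization was the health facility, which formed the clusters". On numbers: "In each country, 20 health facilities were selected and matched in pairs by" several facility characteristics, with 1:1 allocation within each pair. That gives 10 facilities per arm in each country.
- **Sample size.** "Intra-class correlation was estimated at 0.03 for both countries, which will lead to a design effect of 2.45".
- **Data analysis, opening.** The analysis is to follow the "norms for analyzing cluster randomized trials as described in the Consolidated Standards of Reporting Trials guidelines".
- **Data analysis, quantitative, first paragraph.** After the descriptive statistics: "Next, differences between the two study arms will be assessed using chi square test". The sentence names neither a set of variables nor a cluster adjustment. The next sentence says that potential confounders will be assessed.
- **Data analysis, quantitative, second paragraph.** This covers the primary outcome analysis by intention to treat: "The endpoints will be analyzed using a generalized estimating equations multivariable logistic regression model", followed by "The model will adjust the estimates for imbalances in the baseline characteristics".
- **Abstract.** "General estimating equation models that account for clustering will be employed for primary outcome analyzes".
- **Data analysis, quantitative, third paragraph.** Secondary analyses are described as exploring service uptake. No test is named for them.

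**The concern.** An ordinary chi-square test treats every woman as an independent observation. Women attending the same facility share providers, catchment and local practice, and the plan itself allows for this with a non-zero ICC. The test therefore understates the variance of the difference between arms by the design effect, and its p-values are too small.

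The sentence can be read in two ways, and both cause trouble.

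1. **It covers outcomes.** Secondary comparisons such as four or more antenatal visits, counselling received or full infant vaccination could be reported as significant on an invalid test. The article plans about ten publications and presentations to health officials who will decide on policy.
2. **It covers baseline variables.** It would flag too many chance differences. Because the primary model is to adjust for imbalances, those flags could influence which covariates are used.

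**Working it through.** **Inputs from the article**

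- ICC 0.03 and design effect 2.45 (Sample size).
- 20 facilities per country, 10 per arm (Study design, Sample size).
- Planned enrolment of 1,026 in Kenya and 1,076 in Nigeria. Attrition of 20% in Phase 1 and a further 20% by the end of Phase 2 (Sample size).
- Facility delivery of 61% in Kenya and 40% in Nigeria, a 15-point difference, and power of 85% and 80% (Sample size).

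**Assumptions, not in the article:** two-sided 5% significance level, equal cluster sizes, no gain from pair matching.

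**Step 1. Does the plan's own sample size rest on this design effect?** Total = per-arm n × 2 × 2.45 / 0.80, using the usual two-proportion formula.

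- Kenya, 61% vs 76%, 85% power: 171 per arm (pooled variance) gives 171 × 2 × 2.45 / 0.80 = 1,047. The unpooled version gives 168 per arm and 1,029. Stated: 1,026.
- Nigeria, 40% vs 55%, 80% power: 173 per arm (pooled) gives 1,060. Stated: 1,076.

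Both agree to within about 2%, so the plan does size the trial on variance inflated by 2.45.

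**Step 2. Women per facility**

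| Stage | Kenya | Nigeria |
|---|---|---|
| Enrolment | 1,026 / 20 = 51.3 | 1,076 / 20 = 53.8 |
| End of Phase 1 (× 0.8) | 41 | 43 |
| End of Phase 2 (× 0.8 again) | 33 | 34 |

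**Step 3. False-positive rate of the unadjusted test.** With m women per facility, design effect DE = 1 + (m − 1) × 0.03. A test that ignores it has true size 2 × [1 − Φ(1.96 / √DE)].

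- At the stated DE of 2.45: 1.96 / √2.45 = 1.252, giving 21.1%.

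| m | DE | 1.96 / √DE | True size |
|---|---|---|---|
| 33 | 1.96 | 1.400 | 16.2% |
| 34 | 1.99 | 1.389 | 16.5% |
| 41 | 2.20 | 1.321 | 18.6% |
| 43 | 2.26 | 1.304 | 19.2% |
| 51.3 | 2.51 | 1.237 | 21.6% |
| 53.8 | 2.58 | 1.219 | 22.3% |

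Beta-binomial simulation (10 facilities per arm, 40,000 replicates per setting, ICC 0.03) agrees: 19.0% at m = 41 and 22.2% at m = 54 with Phase 1 delivery rates, and 16.3% at m = 33.

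**Step 4. Sensitivity to the ICC (m from 33 to 54).** ICC 0.01 gives 9–11%, 0.02 gives 13–17%, 0.05 gives 22–30%, 0.10 gives 34–43%. Only 0.03 is the plan's value. The others show the range.

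**Step 5. What restores 5%?** In the same simulation at ICC 0.03, a GEE with an ordinary sandwich variance and normal critical values rejects about 8% of the time with 10 facilities per arm. A t-test on facility-level proportions rejects about 5%. Replacing chi-square with GEE removes most of the error. The rest needs a small-sample correction or a facility-level analysis.

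**The case against.** The best defence is that the sentence describes a preliminary step. It sits between descriptive statistics and confounders, ahead of the primary analysis. The GEE sentence refers to endpoints in the plural without limiting them to the primary ones, and the whole section commits to cluster-trial norms. Chi-square also cannot be the complete secondary analysis, since several Table 5 outcomes are averages or scale scores. Secondary methods are commonly left to an analysis plan that is not shown here.

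Much of this stands, and it rules out several stronger readings that a reader might infer:

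- **That the primary outcomes are tested by chi-square.** They are not. The Abstract and the Data analysis section assign them to GEE.
- **That chi-square is the sole test for secondary outcomes.** The text does not say so. The plural in the GEE sentence may include them, although the Abstract ties the cluster-accounting GEE to the primary outcomes.
- **That chi-square results decide the covariates of the primary model.** No sentence says this. The article does not state how imbalance is to be judged.
- **That the error rate approaches 40%.** That needs an ICC of about 0.10, which appears nowhere in the article.

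Effective pair matching would also lower the figures, but the article gives nothing from which to quantify that.

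What the defence does not remove is the sentence itself. A general commitment to cluster-trial norms does not cancel a specific test that departs from them. The conflict is stated in the article and does not depend on detail left to another document.

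**Conclusion.** The point holds within limits. The article prescribes a between-arm test that conflicts with its unit of randomisation, its own ICC and design effect, and its stated analysis norms. The primary inference is not exposed to this error. Preliminary or secondary p-values taken from the step are: about 21% false positives at design effect 2.45, and about 16–22% at ICC 0.03 across 33 to 54 women per facility. The rate would be higher only if the ICC were larger, and would be lower with a smaller ICC or effective matching. If the step serves as a baseline check, about one in five truly balanced variables would be flagged at enrolment cluster sizes.

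**What to change.** 1. Remove the chi-square sentence, or limit the step to descriptive comparison of the arms. Do no significance tests on baseline variables.
2. State that every between-arm outcome test, primary and secondary, accounts for facility clustering. Use either GEE with a small-sample correction suited to 20 facilities per country, or an analysis of facility-level summaries.
3. Replace adjustment for observed imbalances with a covariate set fixed before outcome data are examined. Which covariates to include is for the trial team and can sit in the analysis plan.

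The cost is analysis wording only. Design, data collection and sample size are unchanged. Some secondary p-values will become larger.

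### With 10 facilities per arm in each country, the primary GEE logistic model needs a small-sample variance correction and a paired analysis; run in the usual uncorrected way its 5% test can sit at about 7-8%

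*Protocol article*

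**What the plan says.** The design is fixed under Study design: "In each country, 20 health facilities were selected and matched in pairs by" five listed characteristics, and "The unit of randomization was the health facility, which formed the clusters". Assignment was 1:1 within each pair. The Sample size section was worked out country by country and gives "10 facilities per study arm".

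The analysis is fixed in two places. The Abstract says "General estimating equation models that account for clustering will be employed for primary outcome analyzes". The Data analysis section says "The endpoints will be analyzed using a generalized estimating equations multivariable logistic regression model" and "The model will adjust the estimates for imbalances in the baseline characteristics". It names R as the software and promises reporting "in accordance with norms for analyzing cluster randomized trials as described in the Consolidated Standards of Reporting Trials guidelines".

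The article does not name a variance estimator, working correlation or reference distribution. It does not say whether the model is fitted by country or on both countries together, and the pairs do not appear in the analysis text.

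**The concern.** GEE inference is justified as the number of clusters grows, whatever the number of women. Here the relevant count is 20 per country. With so few clusters the ordinary sandwich variance is biased downward, and a normal critical value ignores the uncertainty in that variance. Both make intervals too narrow. Covariate adjustment, which the plan intends, does not help.

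The matched pairs act in the other direction. If paired facilities resemble each other and the analysis ignores this, the variance of the arm difference is overstated.

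The two effects need not cancel, so the unmodified model has no dependable error rate. This bears on facility delivery in Phase 1 and modern family planning use in Phase 2, and the Dissemination section says the results will go to health officials deciding whether group care enters policy.

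**Working it through.** **Inputs from the article (Sample size, Study design).** 10 facilities per arm per country; ICC 0.03; design effect 2.45; control rates 61% (Kenya) and 40% (Nigeria); difference 15 points; power 85% and 80%; attrition 20%; totals 1,026 and 1,076. **Assumed:** two-sided alpha 0.05, which the article does not state, and the within-pair correlation, which is varied from 0 to 0.75.

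**1. Reproducing the stated sample size.** Two-proportion formula with pooled variance and normal quantiles, times 2.45, divided by 0.8.
- Kenya, 61% vs 76%, 85% power: 171 per arm; 2 × 171 × 2.45 / 0.8 = 1,047 (stated 1,026, 2.1% off).
- Nigeria, 40% vs 55%, 80% power: 173 per arm; 2 × 173 × 2.45 / 0.8 = 1,060 (stated 1,076, 1.5% off).

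Normal quantiles therefore account for the stated totals to within about 2%, without an allowance for few clusters.

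**2. Size of the uncorrected test, analytically.** In the balanced unadjusted case the sandwich variance divides by K² where K(K − 1) would be unbiased, so it is too small by (K − 1)/K = 9/10. The nominal 5% test then has size

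P(|t18| > 1.96 × √0.9) = P(|t18| > 1.859) = 0.079.

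For 40 pooled facilities, P(|t38| > 1.96 × √(19/20)) = 0.064.

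**3. Size by simulation.** 10 facilities per arm, about 41 women analysed in each (1,026 × 0.8 / 20 = 41.0; Nigeria 1,076 × 0.8 / 20 = 43.0), beta-binomial outcomes, ICC 0.03, uncorrelated pairs:

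| Inference | Kenya rate | Nigeria rate |
|---|---|---|
| Uncorrected sandwich, normal reference | 7.8% | 8.0% |
| Kauermann-Carroll, t(18) | 4.9% | 5.0% |
| Mancl-DeRouen, t(18) | 3.9% | 4.0% |

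Coverage is about 92% uncorrected and 95% with Kauermann-Carroll. Over ICC 0.01 to 0.10 and the outcome rates of both phases, uncorrected size stays at about 8%. With unequal cluster sizes and 0 to 6 covariates it was about 7-10% (1,000 runs each, Monte Carlo error about 0.9 points). Pooling both countries gave 6.3%.

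**4. Effect of the matching.** Same setting, with a latent correlation between the two facilities of a pair:

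| Pair correlation | Facility as cluster, pairs ignored, uncorrected | Pair as cluster, uncorrected |
|---|---|---|
| 0 | 7.5-8.1% | 9.4-9.8% |
| 0.1 | 7.1-7.3% | 9.6-9.7% |
| 0.25 | 6.0% | 9.4% |
| 0.5 | 4.2% | 9.5-9.6% |
| 0.75 | 2.6-2.7% | 9.6-9.7% |

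A paired analysis with variance factor 10/9 and t on 9 degrees of freedom held 4.8-5.1% throughout.

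**5. Cost of the correction.**
- Interval width ratio: 2.101 / (1.96 × √0.9) = 1.13.
- Power at the article's design effect of 2.45, Kenya: 1,026 × 0.8 / 2 = 410.4 per arm; / 2.45 = 167.5 effective; SE = √((0.61 × 0.39 + 0.76 × 0.24) / 167.5) = 0.0501; noncentrality 0.15 / 0.0501 = 2.99. This gives 84% with a normal reference (pooled null variance) and 81% with t(18).
- Nigeria: 430.4 / 2.45 = 175.7 effective; SE 0.0527; noncentrality 2.85. This gives 81% and 77%.
- A design effect of 2.45 implies (2.45 − 1) / 0.03 + 1 = 49.3 women per facility, about the enrolled number. At the 41-43 women left after attrition, simulated power with Kauermann-Carroll is 84% (Kenya) and 79% (Nigeria); with Mancl-DeRouen it is 81% and 76%.

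**The case against.** The strongest case against is that the article states nothing wrong. It names GEE, not a variance estimator. R can fit GEE with small-sample corrections, the choice of correction is ordinary SAP content, and neither the SAP nor the full protocol is shown. The article also commits to accepted norms for cluster trials.

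Much of this stands. A reader might infer that the trial does use a large-sample sandwich variance and that its p-values are too optimistic. The documents do not support that: the estimator is unstated, and step 4 shows that even the direction depends on a pair correlation nobody reports.

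A reader might also fear much larger inflation. One simulation with four individual and three facility-level covariates reached 12.6%, but the plan names no facility-level covariates. Its only example is the women's age, and several obvious facility factors were already used for matching.

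Nor does it follow that the stated power is untouched by the correction. That needs a t(18) reference alone, with the design effect recomputed at 2.20 and 2.26 for 41-43 women. It does not hold at the article's 2.45.

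What the objection does not remove is the mismatch between a named method and a fixed cluster count. Ordinary GEE at 20 clusters does not hold its level, citing reporting norms supplies no correction, and a better-calibrated method is available at small cost.

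**Conclusion.** The point holds in conditional form. For a by-country fit with an uncorrected sandwich variance, a normal reference and weakly correlated pairs, a nominal 5% test runs at about 7-8%, with about 92% coverage. Pooling the countries reduces the size to about 6.3%. With pair correlation of about 0.5 or more and pairs ignored, the test is conservative, at about 4% or less. If the pair is made the GEE cluster without correction, it runs at about 9.5%.

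These figures rest on two-sided alpha 0.05, 20% attrition, 41-43 analysed women per facility and beta-binomial outcomes. They barely change over ICC 0.01 to 0.10. The documents do not show that the analysis will be run this way, so this is a weakness in how the primary inference is fixed and no proof that any result is overstated.

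**What to change.** In the Data analysis section, state that the primary GEE analyses in both phases use a small-sample corrected variance, for example Kauermann-Carroll, with a t reference whose degrees of freedom come from the number of facilities: 20 − 2 = 18 per country before any facility-level covariates. Keep facility-level covariates few, since each uses a degree of freedom. Say whether the model is fitted by country or pooled.

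Add an analysis that respects the randomization, such as a pair-stratified permutation test or a paired test on facility-level summaries. The facility-level correction alone would be conservative if the matching worked well.

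Of the two corrections checked, Kauermann-Carroll kept closer to 5%; Mancl-DeRouen over-corrected to about 4% and cost more power.

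The cost is a sentence or two and a software option. The statistical price is intervals about 13% wider and the power loss shown in step 5, which should be disclosed beside the stated 85% and 80%.
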